## **2.4 Randomization**

The 48 eligible senior residential facilities (clusters) were randomized through a central computerized process in a 1:1:1:1 allocation ratio to the 4 intervention groups, with stratification by four regions, (Changzhi , Xi'an, Hohhot and Yangcheng). An independent statistician carried out the randomization after the baseline characteristics had been collected for study sites and individual participants. The allocation codes are kept by the statistician, and only the local staff responsible for the implementation of interventions have been informed. The outcome assessment team is independent of the staff responsible for implementing the interventions

## **2.5 Sample size**

The study was designed to provide at least 80% power (with a 2-sided  $\alpha = 0.05$ ) to detect a net reduction in mean SBP of at least 3.0 mm Hg between groups with either or both interventions compared to control. The power estimate assumed a standard deviation of systolic blood pressure of 18 mmHg based on previous studies, an intra-cluster correlation coefficient of 0.02, and a loss of follow-up rate of 20%, resulting in a sample size of 960 individuals drawn from 48 clusters, each with 20 participants.

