## **2.Trial Purpose**

### **2.1 Primary Purpose**

To compare the effects of using only salt substitutes, only the stepwise salt supply control,

and using both intervention strategies in tandem on reducing the blood pressure of the elderly in Nursing Homes against a control group.

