## 9. Statistical Analysis

### **Baseline Data Analysis:**

Participants will be described with respect to demographic information (age, gender, ethnic group, education, etc.), anthropometrics (weight, height, BMI, etc.), physical examination (SBP, DBP, etc.), life style and diet habits, labs (serum potassium, renal function, urinary sodium, urinary potassium, urinary microalbumin, etc.), comorbidities, medication history at baseline, both overall and separately for the intervention and control groups. Categorical data will be summarized by numbers and percentages. Continuous data will be summarized by mean, SD and range if data are normal and median, IQR and range if data are skewed. We will conduct one-way ANOVA on continuous variables and  $\chi^2$  test on categorical variables to check if the baseline characteristics balanced across randomized groups and to identify potential confounding variables.

**Effect Evaluation:** Results from ITT analysis will be reported as the primary result and the one from PP analysis will be reported as the secondary result.

Primary outcome is the change in SBP from baseline to follow-up

Secondary outcome includes change in DBP from baseline to follow-up, changes in 24-hr urinary sodium and urinary microalbumin; the risk of developing cardiovascular events

We will use multilevel mixed-effects model to control the cluster effect and confounding variables. We will compare the difference of changes in blood pressure before and after the intervention between SS and non-SS, SSSC and non-SSSC, SS + SSSC and SS only or SSSC only respectively.

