### **3.1 Confidence intervals and p values**

All applicable statistical tests will be 2-sided and will be performed using a 5% significance level. All confidence intervals presented will be 95% and two-sided.

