#### **5.1.1 Primary analysis**

The primary analysis will be performed in FAS dataset. The results will be regarded as the main findings.

A pre-specified linear mixed effects model will be performed to model repeated measures of SBP of the same individual over time. The model will include intervention status and baseline SBP as fixed effects, as well as cluster and time as random effects. Separated models will be built for each intervention, either SS alone or SSSC alone. The model would be:

$$y_{ijt} = \beta_0 + \mu_{1i} + \mu_{2j} + \beta_1 x_{ij} + \beta_2 c_{ij} + \beta_3 t + e_{ijt}$$

$$e_{ijt} \sim N(0, \sigma_e^2)$$

$$\mu_{1i} \sim N(0, \sigma_{\mu 1}^2)$$

$$\mu_{2j} \sim N(0, \sigma_{\mu 2}^2)$$

Where  $i$  represents the  $i^{\text{th}}$  subjects,  $j$  represents the  $j^{\text{th}}$  cluster (facility),  $t$  represents time point  $t$ ,  $y_{ijt}$  is the SBP measured for subject  $i$  in cluster  $j$  at time  $t$  (follow-up month), baseline SBP will not be included in  $y_{ijt}$ ;  $\beta_0$  is the mean outcome in the control group at baseline;  $\mu_{1i}$  is an individual random effect to allow for multiple repeats per person;  $\mu_{2j}$  is a cluster random effect on baseline SBP to allow for between-cluster heterogeneity;  $x_{ij}$ , the predictor of interest, either SS or SSSC, is an indicator of the intervention for subject  $i$  in cluster  $j$  (1 indicates receive intervention while 0 indicates not receive intervention);  $\beta_1$ , the coefficient of interest, is the effect coefficient of intervention;  $c_{ij}$  is the baseline SBP measured for subject  $i$  in cluster  $j$ ;  $e_{ijt}$  is the random error for the measurement of subject  $i$  in cluster  $j$  at time  $t$ .

The estimation of  $\beta_1$ , its 95% confidence interval and the corresponding  $p$  value will be reported in **Table 2**.

We will also evaluate the interaction between SS and SSSC in lowering SBP during study period. If the effect of both interventions do exist, we will add interaction term in the above model to test the interaction between SS and SSSC. The model would be:

$$y_{ijt} = \beta_0 + \mu_{1i} + \mu_{2j} + \beta_1 x_{1ij} + \beta_2 x_{2ij} + \beta_3 x_{1ij} * x_{2ij} + \beta_4 c_{ij} + \beta_5 t + e_{ijt}$$

$$e_{ijt} \sim N(0, \sigma_e^2)$$

$$\mu_{1i} \sim N(0, \sigma_{\mu 1}^2)$$

$$\mu_{2j} \sim N(0, \sigma_{\mu 2}^2)$$

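### Protocol 2.1 and the power sentence in SAP 2.5 name comparisons with the control arm, but the primary model estimates factorial margins; on the stated inputs none of these comparisons has 80% power for 3.0 mmHg

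*Supplement*

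**What the plan says.** **Protocol V1.4, 2.1 (primary purpose).** "To compare the effects of using only salt substitutes, only the stepwise salt supply control", and the two together, against a control group. This is a set of arm-v-control comparisons.

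**SAP 2.5 (sample size).** "The study was designed to provide at least 80% power" (two-sided 5%) "to detect a net reduction in mean SBP of at least 3.0 mm Hg between groups with either or both interventions compared to control". This is the only power statement in the SAP.

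**Protocol V1.4, 9 (effect evaluation).** Changes in blood pressure are compared "between SS and non-SS, SSSC and non-SSSC, SS + SSSC and SS only or SSSC only respectively". The first two are margins; the last sets the combination against each single strategy.

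**Protocol V1.4, 10.** Power is given for SS (3.0 mmHg, 0.80) and for SSSC (4.0 mmHg, 96.6%), with a table whose margins are 480 v 480.

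**SAP 5.1.1 (primary analysis).** "Separated models will be built for each intervention, either SS alone or SSSC alone". The indicator is 1 if the facility's residents receive the intervention and 0 if they do not. A second model with an interaction term is added only if both interventions turn out to have an effect; no criterion for that is given. From it the two main coefficients and the interaction coefficient are reported. SAP Table 2 has one SS column, one SSSC column and an interaction p value. SAP Figure 3 shows SS v non-SS and SSSC v non-SSSC.

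**SAP 5.9 (changes from protocol).** It has no entry for the combination-v-single-strategy contrasts of protocol 9, which the SAP does not list.

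**The concern.** In SAP 5.1.1 the facilities coded 0 for SS include those on SSSC only, and those coded 0 for SSSC include those on SS only. The primary coefficient is therefore a marginal effect over 24 v 24 facilities. It is not the effect of one strategy against the control arm (12 v 12), nor the effect of any intervention against control (36 v 12 if SAP 2.5 is read as one pooled contrast).

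Two things are at stake. If the interventions interact, the primary result will not answer the purpose in protocol 2.1, and the analysis that could answer it may never be run. And the stated power is attached to a comparison that is not tested.

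**Working it through.** **Inputs.** SAP 2.5: "a standard deviation of systolic blood pressure of 18 mmHg based on previous studies"; ICC 0.02; 20% lost to follow-up; 48 facilities of 20. SAP 3.1: "All applicable statistical tests will be 2-sided and will be performed using a 5% significance level". Protocol 10: 16 evaluable per facility (20 × 0.8). SAP 2.4: allocation 1:1:1:1, so 12 facilities per arm.

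**Formula.** Design effect = 1 + (16 − 1) × 0.02 = 1.30. SE = 18 × √[1.30 × (1/(16k₁) + 1/(16k₂))] for k₁ v k₂ facilities. Power is from the noncentral t with k₁ + k₂ − 2 df.

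**The plan's own figures first.** With 48 facilities *per side*, power is 80.9% at 3.0 mmHg, 16 is the smallest facility size that reaches 80%, and power at 4.0 mmHg is 96.6%. These match protocol 10. With 48 facilities *in total*, as the trial has, no comparison gives them:

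| Comparison | Facilities | SE (mmHg) | Power at 3.0 | Power at 4.0 |
|---|---|---|---|---|
| One arm v control (protocol 2.1) | 12 v 12 | 2.10 | 27.8% | 44.7% |
| Any intervention v control (SAP 2.5, read as pooled) | 36 v 12 | 1.71 | 40.4% | 62.9% |
| Margin (SAP 5.1.1) | 24 v 24 | 1.48 | 50.9% | 75.3% |

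The normal approximation gives 29.9%, 41.9% and 52.6% at 3.0 mmHg. If all 20 per facility were retained it gives 34.2%, 47.8% and 59.4%.

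**Do the quantities differ?** Take the protocol's effects, −3 for SS and −4 for SSSC. Let A be an assumed antagonism, so that the cell means relative to control are 0, −3, −4 and −7 + A.

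- SS margin = [(−3 − 0) + (−7 + A + 4)]/2 = −3 + A/2
- SSSC margin = −4 + A/2
- Any intervention v control = (−14 + A)/3

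| A (assumed) | SS only v control | SS margin | SSSC only v control | SSSC margin | Any v control |
|---|---|---|---|---|---|
| 0 | −3.0 | −3.0 | −4.0 | −4.0 | −4.67 |
| 1 | −3.0 | −2.5 | −4.0 | −3.5 | −4.33 |
| 2 | −3.0 | −2.0 | −4.0 | −3.0 | −4.00 |
| 3 | −3.0 | −1.5 | −4.0 | −2.5 | −3.67 |

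At A = 0 the arm-v-control and marginal effects coincide. Any intervention v control differs from both margins in every row shown.

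**How often would the interaction model be fitted?** Suppose an effect counts as present when its margin has p < 0.05 (an assumption; the SAP gives no rule). With SE 1.48 and the normal approximation, the two margins reach this with probability 0.526 and 0.771 at A = 0, a product of about 41%. At A = 3 the probabilities are about 0.17 and 0.39, a product of about 7%. The model is least likely to be fitted where the interaction matters most.

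**The case against.** The strongest reply is that the operative plan is consistent. SAP 2.1 sets each intervention against its own absence (salt reduction against usual supply, salt substitute against regular salt), which is naturally a margin. Protocol 9 and 10, the SAP 5.1.1 indicator, Table 2 and Figure 3 all fit margins. SAP 2.5 repeats the inputs of protocol 10 and may simply be a loose summary of it. This stands. A reader might infer that the primary comparison is defined in three incompatible ways and that the estimand is open. The documents do not support that: the mismatch lies in protocol 2.1 and SAP 2.5. The word *alone* in SAP 5.1.1 is untidy, but the definition of the indicator settles its meaning. Without interaction, the aim in protocol 2.1 and the margins agree for the single strategies.

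It can also be said that arm effects are partly planned. The main coefficients of the interaction model are SS only and SSSC only against control, and SAP Figure 2 plots all four arms. That is true, but the model is conditional, the combination against control is not among the reported estimates, and Table 2 has no column for any such contrast.

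Finally, the primary model adjusts for baseline SBP and uses up to four follow-up measurements, so the SEs above are not those of the planned analysis. This stands too. The documents give no correlation from which to work out the gain. For 80% at a margin the effective SD would have to fall from 18 to about 13.0 mmHg, a 48% cut in variance (normal approximation).

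**Conclusion.** The point holds as a mismatch between two sentences and the analysis, together with a power figure that fits none of the comparisons. Where there is interaction, the primary estimate departs from the arm-v-control effect by half of it: 0 to 1.5 mmHg for an assumed antagonism of 0 to 3 mmHg. The documents give no value for the interaction, so this is a range and not a forecast.

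On the stated inputs, power for 3.0 mmHg is about 28%, 40% or 51% depending on the comparison, taking a single unadjusted measurement. A reader might infer that the shortfall from 80% comes from naming the wrong comparison. It does not: the margins fall short as well, and the protocol's figures reproduce only with 48 facilities per side. Nor do these figures show that the planned repeated-measures model has 51% power; that cannot be computed from the documents.

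**What to change.** 1. In protocol 2.1 and SAP 2.5, name SS v non-SS and SSSC v non-SSSC as the primary comparisons. Use the same terms in SAP 5.1.1 and 5.2.2 in place of the wording that describes each strategy as alone.
2. Restate the power for the margins: about 51% at 3.0 mmHg and 75% at 4.0 mmHg on the stated inputs. Alternatively, recalculate with a stated and justified gain from baseline adjustment and repeated measures. Do not carry the 80% over.
3. Fit the interaction model whatever the main effects show. From it report each single arm and the combination against control, with 95% CIs, labelled as secondary.
4. Record in SAP 5.9 that the combination-v-single-strategy contrasts of protocol 9 were dropped, or reinstate them.

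The cost is wording, one power recalculation and a few contrasts from data already held; the primary model does not change. The downside is that the arm-v-control contrasts are imprecise (SE about 2.1 mmHg before any gain from baseline adjustment and repeated measures) and must be presented as such.

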## **2.6 Framework**

Both primary and secondary aim are testing for difference.

## 2.7 Statistical interim analysis and stopping guidance

Interim analyses are not planned.

## 2.8 Timing of final analysis

The first main report of the trial will be prepared for the evaluation of efficacy and safety of sodium reduction intervention when every participant has reached 24 months follow-up and data for the primary endpoint has been received and cleaned (anticipated to be End of March, 2021).

## 2.9 Timing of outcome assessments

The schedule of the study procedure and the expected visit windows are given in **Table 1** as below.

**TABLE 1 TIME-LINE FOR FOLLOW-UP**

| Time-point
Items            | Preparation | Base line | Follow-up |          |          |          |                     |          | Quit |
|--------------------------------|-------------|-----------|-----------|----------|----------|----------|---------------------|----------|------|
|                                |             |           | 6-month   | 12-month | 18-month | 24-month | When ever necessary | Referral |      |
| Informed consent               | √           |           |           |          |          |          |                     |          |      |
| Eligible criteria confirmation | √           |           |           |          |          |          |                     |          |      |
| Basic information              | √           |           |           |          |          |          |                     |          |      |
| Demographics                   |             | √         |           |          |          |          |                     |          |      |
| Lifestyle                      |             | √         |           |          |          |          |                     |          |      |
| Diet survey                    |             | √         | √         | √        | √        | √        |                     |          | √    |
| Past history                   |             | √         |           |          |          |          |                     |          |      |
| EQ-5D                          |             | √         |           | √        |          | √        |                     |          | √    |
| Anthropometrics                |             | √         |           |          |          | √        |                     |          | √    |
| Vital signs                    |             | √         | √         | √        | √        | √        |                     |          | √    |
| Complete blood count           |             | √         |           |          |          | √        |                     |          | √    |
| Glucose and lipid panel        |             | √         |           |          |          | √        |                     |          | √    |
| 24-hour urine                  |             | √         |           |          |          | √        |                     |          | √    |
| Ophthalmoscopy                 |             | √         |           |          |          | √        |                     |          | √    |
| Antihypertensive meds          |             | √         | √         | √        | √        | √        |                     |          | √    |
| Hospitalization information    |             | √         |           |          |          |          |                     | √        |      |
| Adverse event                  |             |           |           |          |          |          | √                   |          |      |
| Signature page                 |             |           |           |          |          | √        |                     |          | √    |

## 3. Statistical Principles

The analysis will be conducted by intention-to-treat.

### **3.1 Confidence intervals and p values**

All applicable statistical tests will be 2-sided and will be performed using a 5% significance level. All confidence intervals presented will be 95% and two-sided.

### **3.2 Adherence and protocol deviations**

Compliance is assessed mainly based on the number of facilities that have adhered to the protocol throughout the study period. Other information that helps to assess compliance includes: 1) the 24hr sodium and potassium excretion; 2) site monitoring data on the 3-monthly checking on the salt supply, in against to the goal of consumption set by the interventionist according to the study plan; 3) degree of satisfaction with food prepared at the facilities. Descriptive statistics on the percent of compliant facility (N (%)) will be summarized.

A protocol deviation is defined as a failure to adhere to the protocol. The following are pre-specified definition of protocol violations:

- 1) For all facilities: dropping out of the study before the end of trial
- 2) Failure to adhere to intervention as planned:
  - a. For facilities assigned to salt substitute intervention: stopping using the salt provided by researchers before the end of trial
  - b. For facilities assigned to stepwise salt reduction strategy intervention: refusal to comply with the stepwise strategy

### **3.3 Analysis populations**

#### **Full-analysis set (FAS):**

For the analysis of the primary outcome (SBP), FAS will include all eligible randomized subjects with baseline SBP measured and at least 1 post-baseline measurement on SBP, according to the intervention they were randomized to receive. No imputation will be used for primary outcome in main efficacy analysis.

For the analysis of clinical events, FAS will include all eligible randomized subjects with baseline SBP measured, follow-up SBP measurements are not required.

**Per-protocol analysis set (PPS):**

PPS consists all subjects who: 1) meet the above criteria for FAS 2) do not experienced major protocol deviation during the study period.

**Safety set (SAS):**

SAS will consist of all randomized subjects who: 1) have baseline serum potassium measured 2) have received at least one month of study intervention, regardless of their eligibility. Subject will be analyzed according to the intervention they actually received.

### 3.4 Missing data

No imputation will be conducted for primary analysis of primary outcome, secondary outcomes and safety outcomes.

For survival analysis, those who loses to follow-up will be regarded as right-censored and the censoring date will be the date of last encounter. If the date of occurrence of an event is not recorded, it will be imputed as the median of the date of last follow-up and the one when event reports.

For sensitivity analysis of SBP difference from baseline to 24-month SBP, 24-month SBP will be imputed using multiple imputation. The model will be:

$$Y_i = \beta_0 + \sum \beta_i X_i + e_i$$
$$e_i \sim N(0, \sigma_e^2)$$

Where  $Y_i$  is the SBP for subject  $i$  at month 24;  $\beta_0$  is the intercept;  $X_i$  is the variable for imputation;  $e_i$  is the random error.

Variables for multiple imputation of 24-month SBP includes SBP, DBP and pulse at baseline, 6 months, 12 months and 18 months, as well as residential facilities, center, age, gender, education, BMI, past history of hypertension, diabetes and coronary artery disease, lifestyle information, medication use in baseline and follow-up.

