## **6.Outcome Measure**

### **6.1 Primary Outcome**

The primary outcome for the study is the difference of SBP between baseline and at 24 months of intervention.

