## 10. Sample Size Calculation

The research hypothesis is that the "salt substitute intervention would significantly reduce the systolic blood pressure of patients with hypertension", with the test power of 0.80 and the significance level at 0.05. According to previous studies, consuming salt substitutes for a prolonged period can lower the systolic blood pressure of patients with hypertension by roughly 2~5mmHg. This research hypothesizes that the systolic blood pressure of the elderly participants would decrease by 3.0mmHg, with a standard deviation of 18mmHg. Since the number of groups is 48 and the intra-group correlation coefficient is 0.02, 16 participants are needed in every group calculated by NCSS-PASS software. In addition, considering that about 20% of the participants might be lost to follow-up or be removed from the research due to non-compliance, it is finally determined that 20 participants will be included in each nursing home, for a total of 960 participants across 48 nursing homes.

Based on the sample size calculated above, the sample size for the four intervention groups is as follows:

|                   |     | SS intervention |     |       |
|-------------------|-----|-----------------|-----|-------|
|                   |     | Yes             | No  | Total |
| SSSC intervention | Yes | 240             | 240 | 480   |
|                   | No  | 240             | 240 | 480   |
| Total             |     | 480             | 480 | 960   |

For the other intervention strategy, it can be estimated from the previous research experience that the SSSC intervention strategy can reduce the systolic blood pressure of the elderly by 4.0mmHg. With the significance level, number of groups, and intra-group correlation coefficient constant, and based on the sample size calculated above, it can be concluded that the power of applying this intervention strategy to reducing systolic blood pressure by 4.0mmHg will be 96.6%.

Given the potential changes of actual systolic blood pressure difference during the trial and the number of participants recruited from each facility, the changes to the trial power will follow the trend below:

[figure not shown]

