## 5.7 Sensitivity analysis

Sensitivity analysis will be performed as below:

- 1) the per-protocol analysis of outcomes
- 2) to assess the effect of intervention on SBP change from baseline to 24-month, we will first use multiple imputation to impute missing value at 24-month. Then we will perform mixed model to account for clustering. The model would be:

$$y_{ij} = \beta_0 + \mu_j + \beta_1 x_{ij} + \beta_2 c_{ij} + \sum BZ_{ij} + e_{ij}$$

$$e_{ij} \sim N(0, \sigma_e^2)$$

$$\mu_j \sim N(0, \sigma_{\mu_j}^2)$$

Where  $i$  represents the  $i^{\text{th}}$  subjects,  $j$  represents the  $j^{\text{th}}$  cluster (aka. facility),  $y_{ij}$  is the SBP difference measured for subject  $i$  in cluster  $j$ ;  $\beta_0$  is the mean outcome in the control group at baseline;  $\mu_j$  is a cluster random effect to allow for between-cluster heterogeneity;  $x_{ij}$  is an indicator of the intervention for subject  $i$  in cluster  $j$  (1 indicates receive intervention while indicates not receive intervention),  $\beta_1$  is the effect coefficient of intervention;  $c_{ij}$  is the baseline SBP measured for subject  $i$  in cluster  $j$ ;  $Z_{ij}$  is the covariates other than baseline SBP;  $e_{ij}$  is the random error for the measurement of subject  $i$  in cluster  $j$ .

- 3) Since it may take several months for SSSC to take effect, we will conduct a sensitivity analysis for SSSC after excluding data in 6-month.
- 4) Since more missing data was observed in Xi'an, we will perform a sensitivity analysis after excluding participants from Xi'an.
- 5) For the analysis of urine electrolytes, a sensitivity analysis will be conducted after excluding possibly incomplete 24h urine collection. Incomplete 24h urine sample is defined as urine volume < 500ml/d.
- 6) For the analysis of events, a sensitivity analysis will be conducted on all randomized participants, regardless of the availability of the baseline BP measurements.

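### The imputation of 24-month SBP treats facility as an ordinary predictor while the analysis treats it as random, so the standard errors of that one sensitivity analysis are modestly too large

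*Supplement*

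**What the plan says.** The protocol (V1.4, section 6.1) states: "The primary outcome for the study is the difference of SBP between baseline and at 24 months of intervention". The SAP (5.9) moves the primary outcome to SBP over all follow-up visits because of missing data from deaths and departures, and its primary model (5.1.1) uses no imputation.

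The change to month 24 survives as a sensitivity analysis. SAP 3.4 states: "For sensitivity analysis of SBP difference from baseline to 24-month SBP, 24-month SBP will be imputed using multiple imputation". The formula given there has an intercept, a sum of predictor terms and a single residual indexed by subject only. The predictors are SBP, DBP and pulse from baseline to month 18, "as well as residential facilities, center, age, gender, education, BMI, past history of hypertension, diabetes and coronary artery disease", lifestyle, and medication use. There is no facility-level random term, and SS and SSSC are not named.

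SAP 5.7 item 2 describes the step after imputation: "Then we will perform mixed model to account for clustering". That model does carry a facility random effect, with baseline SBP and covariates as fixed effects.

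**The concern.** Facilities were randomised, so the precision of each contrast rests on the variation between facility means. In a linear model with a single error term, facility can enter only as a set of indicator (fixed) terms. The SAP does not use the word fixed, but its formula leaves no other reading.

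With roughly 16 observed residents per facility and a small ICC, the indicators make each imputation draw every facility's level from its own few residents, with no pooling. All imputed residents of a facility share that draw. The noise inflates the between-facility variance in each completed data set, and Rubin's between-imputation term counts it again.

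Readers will use this analysis to judge whether changing the primary endpoint altered the conclusion. An overstated standard error could make a real effect look fragile, and the distortion grows with missingness, which is the problem the analysis is meant to address.

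**Working it through.** **Inputs from the documents.** Protocol section 10: an assumed SBP effect of 3.0 mmHg and an SD of 18 mmHg; 20 enrolled per facility; about 20% loss; "with the test power of 0.80 and the significance level at 0.05"; and, for the clusters, "Since the number of groups is 48 and the intra-group correlation coefficient is 0.02, 16 participants are needed in every group". SAP 3.1: "All applicable statistical tests will be 2-sided and will be performed using a 5% significance level". SAP 2.4: 1:1:1:1 allocation, hence 24 v 24 facilities per factorial contrast.

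**Assumed, because the documents give no figure.** The share p of month-24 values missing (20% is the plan's loss rate; 30-40% is illustrative), and R², the share of within-facility variance explained by the other imputation predictors (0 to 0.75).

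**The plan's own power figure.** SE = 18 × sqrt(2 × (1 + 15 × 0.02) / (24 × 16)) = 1.48 mmHg. Power at 3 mmHg is then 52.6% (normal) or 50.9% (t, 46 df). The stated 80% and 96.6% come out only with 48 facilities per side (80.9% and 96.6%, t version). That is a separate matter. It is noted here because it explains why the simulated powers below start well under 80%.

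**Closed form for the standard error** (in units of total variance, m = 20):
- Drawing noise in a facility mean: B = (1 − ICC)(1 − R²)/m × p/(1 − p).
- True variance of the facility mean: T = ICC + (1 − ICC)/m + B.
- Rubin's variance after facility-indicator imputation: T + 2B.
- SE ratio: r = sqrt((T + 2B)/T).

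| p | R² | B | T | T + 2B | r |
|---|---|---|---|---|---|
| 20% | 0 | 0.0123 | 0.0813 | 0.1058 | 1.14 |
| 20% | 0.5 | 0.0061 | 0.0751 | 0.0874 | 1.08 |
| 20% | 0.75 | 0.0031 | 0.0721 | 0.0782 | 1.04 |
| 35% | 0 | 0.0264 | 0.0954 | 0.1482 | 1.25 |
| 35% | 0.5 | 0.0132 | 0.0822 | 0.1086 | 1.15 |
| 35% | 0.75 | 0.0066 | 0.0756 | 0.0888 | 1.08 |

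**Power, starting from the planned 80%.** Φ(2.80/r − 1.96) treats the whole inflation as lost precision. Φ(2.80 − 1.96r) inflates only the reported SE.
- 20% missing, R² = 0, 0.5, 0.75: 69.0%, 73.8%, 76.7% by the first, or 71.4%, 75.4%, 77.6% by the second. The loss is about 11 points at most and about 3 at least.
- 35% missing, R² = 0, 0.5, 0.75: 61.3%, 68.4%, 73.4% by the first, or 64.0%, 70.8%, 75.1% by the second. The largest loss is about 19 points.

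**Simulation with the SAP 5.7 mixed model** (REML, 20 imputations, Rubin's rules, 3 mmHg effect, 48 × 20, ICC 0.02; 900-1,200 runs per row):

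| Missing | Within-person correlation | Mean SE, indicators v random intercept | Power, indicators v random intercept |
|---|---|---|---|
| 20% | 0.5 | 1.44 v 1.28 (+13%) | 52% v 61% |
| 20%, month 24 only | 0.7 | 1.22 v 1.10 (+10%) | 68% v 74% |
| 30% | 0.5 | 1.61 v 1.35 (+19%) | 43% v 56% |
| 40% | 0.5 | 1.81 v 1.43 (+26%) | 33% v 52% |

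The mean estimate was about −3.0 in every row, so there is no bias. In these rows the type I error was 1-3% with indicators and 4-5% with the random intercept. The random-intercept SE was calibrated (mean SE over empirical SD 0.99-1.01).

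A separate simulation used a facility-mean t test with 600 runs per cell. Its SE ratios were 1.08-1.16 at 20% missing (power 8-11 points lower than with a random intercept) and 1.17-1.25 at 35% (15-17 points lower).

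**The case against.** The strongest reply is that the SAP does not ignore clustering. Facility indicators keep the between-facility differences and err on the conservative side, and the analysis concerned is one item in a sensitivity list. All of that stands, and it limits the severity.

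The size is also conditional:
- **Predictors.** The listed set is rich (SBP, DBP and pulse at four time points, plus medication). If it explains about 75% of the within-facility variance, the excess at 20% missing is only about 4%.
- **Facility size.** Twenty per facility is a minimum. At 40 per facility the excess at 20% missing is 6-11% (R² 0.5 to 0).
- **ICC.** At 0.05 with 20 per facility and 20% missing, the excess is 6-10% (R² 0.5 to 0).
- **Missing rate.** The plan's 20% includes removals for non-compliance, whom an intention-to-treat analysis keeps if they are measured. At 10% missing and R² 0.5 the excess is about 4%.

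A reader might infer that omitting SS and SSSC from the predictor list, or listing center beside facility, biases the result. It does not: the facility indicators already contain both arms, their interaction and region. A reader might also infer that the SE excess is 25% whatever the data, or that the trial's main finding is affected. The first needs an assumed 35% missing and uninformative predictors. The second is wrong, because the primary model uses no imputation.

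What remains is that the rule as written gives error bars that are too wide at every setting examined.

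**Conclusion.** Wrong as written, minor severity. The imputation model and the analysis model treat facility differently, and the reported standard error is too large as a result. Under the plan's figures (20 per facility, ICC 0.02, 20% loss) the excess is about 4-14%, costing about 3-11 points of power. At an assumed 35% missing it is about 8-25%, and up to about 17-19 points. The low ends assume that the other predictors explain about 75% of the within-facility variance; the high ends assume that they explain none.

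The error cannot move the estimate or create a false positive. It is confined to the sensitivity analysis in SAP 5.7 item 2. That analysis is nevertheless the SAP's only model of the protocol's baseline-to-24-month change; the other month-24 display, Figure 2, plots means and intervals by arm. The SAP cites high mortality and departures, and more missing data in Xi'an, but gives no rate, so the actual size cannot be fixed from the documents.

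**What to change.** In SAP 3.4, replace the facility predictor with a facility random intercept, so that the imputation matches 5.7 item 2. In the same edit, add SS, SSSC and SS × SSSC as fixed effects. Once the facility indicators go, nothing else in the imputation model carries the randomised contrast, so this is necessary. Keep region (center) as a fixed effect and keep the other listed covariates.

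SAP 5.8 already allows R or Stata, either of which can fit this model. The cost is a wording change, a different imputation routine and a convergence check. The random intercept also assumes normally distributed facility effects, as the analysis model already does. No new data or participants are needed.
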